		**Average size of the clusters**		
		20	30	40
**ICC**	0.02	10	8	8
	0.03	12	10	10
	0.04	12	10	10
	0.05	14	*12*	10

A sample size of six clusters per group with 30 individuals per cluster achieves 80% power to detect a difference of 3.2 between the group means when the intracluster correlation is 0.05 using a Two-Sided *T*-test with a significance level of 0.05.

### Recruitment of hospitals

Based on the cluster size calculation, 10 to 12 hospitals with one or more acute geriatric wards must be recruited. In order to recruit these hospitals, the study has been presented at three geriatric meetings. Shortly after these meetings information letters were sent to geriatricians. Geriatricians who were interested in participating were contacted by the researcher to make an appointment to explain and discuss the study and to sign an agreement of participation form. If geriatricians did not spontaneously contact the researcher, the researcher took the initiative herself to contact the geriatricians by phone about their interest and possible participation.

### Randomization

At the end of the baseline assessment the included hospitals with one or more participating acute geriatric wards will be randomly assigned to the intervention group (implementing the Care Programme for the Last Days of Life) or to the control group (usual care).

As the number of clusters to be randomized is considerably smaller than in trials where the unit of randomization is the patient, there is a chance of baseline imbalance between the randomized groups. The risk of baseline differences can be reduced using pair-matched randomization [33]. Hospitals will be matched in comparable pairs in terms of 1) the number of deaths per year for the participating geriatric wards, and 2) the motivation of the participating wards in terms of the number of patients from whom they will acquire informed consent for participation in the baseline measurement period. Information related to the number of deaths and motivation per hospital will be sent to a statistician outside the research group, who will then match the pairs and randomize the hospitals into the experimental and control group using a random number generator.

### Statistical analysis

All data collected through the three different questionnaires will be stored and collected in Ghent University Hospital using IBM SPSS Statistics. Data cleaning will be performed via SPSS syntax operations. All statistical tests will be done two-tailed with 95% confidence intervals. A p-value <0.05 will be considered statistically significant.

#### Descriptive statistics

Cluster and patient characteristics will be reported as mean and standard deviation (SD) or frequency and percentage respectively for continuous and categorical variables. The distribution of characteristics of clusters allocated as experimental or control hospitals will be compared with the Student *t*-test (for continuous variables), with non-parametric tests (for ordinal variables) and with the Pearson Chi-square (for binary or nominal variables).

#### Multivariable analysis

Our primary aim is to detect any differences in the EOLD-SM [26] and EOLD-CAD [26] between those dying in the intervention wards and those dying in the control wards. The primary statistical analysis will be by intention-to-treat, using multi-level models, taking into account clustering by hospitals. Because these primary outcomes are continuous, hierarchical linear models will be used which will be adjusted for the average level of quality of life and quality of care provided to the baseline assessment. This method of analysis will also be used for our secondary outcome measures. For the assessment of categorical secondary outcomes, the hierarchical logistical model will be used.

### Informed consent procedure

In order to guarantee privacy for patients whose data is collected in the study, certain procedures are necessary. As the Central Ethics Committee requires that data can only be collected from deceased patients who have given informed consent prior to the study, written informed consent to use personal data for the study will be requested by a nurse from each patient at the time of admission of the patient to the ward. If the patient is lacking in capacity, written informed consent will be requested from a family carer. Questionnaires will be filled in only for patients with informed consent at admission.

The physician and the nurse who were closely involved in the care of a deceased patient will be asked to fill in a questionnaire about the patient. If one of them refuses to complete the questionnaire the nurse who is responsible for the study on the ward will pass the questionnaire to another nurse or physician. A closely involved family carer will also be asked to fill in a questionnaire about their deceased relative and about their own experiences of care in the dying phase. In order for the researcher to be allowed to send a questionnaire to the family carer, a nurse will ask informed consent of the family carer shortly after the death of the patient. Family carers who give informed consent will be asked to sign a written informed consent form including their contact details. If the nurse in the hospital is unable to ask informed consent from the family carer shortly after the death of the patient, the hospital will send an informed consent form by post to the family carer two weeks after the death of the patient asking permission for the researcher to contact them. Family carers who give informed consent to being contacted by the researcher will be sent a questionnaire six weeks after the patient’s death. Family carers are also asked for their informed consent to fill in the questionnaire.

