To improve the quality of care at the end of life in the geriatric hospital population we developed and successfully piloted the Care Programme for the Last Days of Life ([name], [name], [name], [name], [name], [name], [name]: Development of the care programme for the last days of life for older patients in acute geriatric hospital wards: a phase 0–1 study according to the Medical Research Council Framework, submitted; [name], [name], [name], [name], [name], [name]: Feasibility and preliminary effects of the Care Programme for the Last Days of Life in an older acute hospital population: mixed-methods study of the success of implementation and staff perceptions, in preparation). This programme is based on the Liverpool Care Pathway (LCP) programme, taking into account the concerns regarding the LCP raised in the UK and adapted to the geriatric hospital population and setting ([name], [name], [name], [name], [name], [name], [name]: Development of the care programme for the last days of life for older patients in acute geriatric hospital wards: a phase 0–1 study according to the Medical Research Council Framework, submitted). The Care Programme essentially aims to raise awareness among geriatric health care staff of the importance for improving end-of-life care and to prepare them for a change in end-of-life care, to train staff in delivering good end-of-life care with the support of a multi-professional document called the Care Guide for the Last Days of Life, to support dying geriatric patients with the Care Guide for the Last days of Life, to regularly evaluate the delivered end-of-life care and support and to further educate the staff in delivering optimal end-of-life care. The Care Programme consists of the following documents: (1) the Care Guide for the Last Days of Life, (2) supportive documentation and (3) an implementation guide (Figure 1).

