### General procedures of the cluster RCT

First, a one-year baseline assessment will be conducted in all participating acute geriatric wards of participating hospitals. During that period care will be provided as usual. At the end of the baseline assessment all participating hospitals with one or more participating wards will be randomized into intervention or control groups. In the intervention group the Care Programme for the Last Days of Life will be implemented over a six-month period with the support of an implementation guide (Figure 2). After the implementation period, the intervention group will conduct a one-year post-intervention assessment during which the Care Guide for the Last Days of Life will continue to be used. The control group will continue to provide care as usual and will conduct a one-year post-intervention assessment directly following the one-year baseline assessment (Figure 2).

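### Outcome-year patients and family carers are consented after randomisation by ward nurses who can be expected to know the arm, and the stated primary model would not remove a case-mix difference that arises after allocation

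*Protocol article*

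**What the plan says.** Timing. The section General procedures of the cluster RCT says: "At the end of the baseline assessment all participating hospitals with one or more participating wards will be randomized into intervention or control groups". The outcome year follows, directly in control hospitals and after six months of implementation in intervention hospitals.

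Entry of patients. Under Informed consent procedure, "written informed consent to use personal data for the study will be requested by a nurse from each patient at the time of admission". A family carer is asked if the patient lacks capacity. Consent decides who is analysed: "Questionnaires will be filled in only for patients with informed consent at admission".

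Entry of family carers. In the same section, "a nurse will ask informed consent of the family carer shortly after the death of the patient". If the nurse cannot ask, the hospital posts a form two weeks after the death. Table 2 shows that nurses and family carers each rate both primary scales, EOLD-SM and EOLD-CAD.

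Consent yield. The Randomization section pairs hospitals on annual deaths and on "the motivation of the participating wards in terms of the number of patients from whom they will acquire informed consent", measured in the baseline period.

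The programme. According to the Background, it "aims to raise awareness among geriatric health care staff of the importance for improving end-of-life care" and prepares and trains staff. Table 1 describes how staff are informed, trained, coached and audited.

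Analysis. Under Multivariable analysis, "hierarchical linear models will be used which will be adjusted for the average level of quality of life and quality of care", taken from the baseline assessment. No patient-level covariate is named. Under Descriptive statistics, "Cluster and patient characteristics will be reported as mean and standard deviation" or as frequencies, without a list of the characteristics. The limitations in the Discussion do not mention recruitment after randomisation.

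**The concern.** In a cluster trial, randomisation protects the comparison of hospitals. It protects the comparison of patients only if patients enter the analysis in the same way in both arms. Here every outcome-year patient enters after allocation, through a request made by ward staff who in one arm have been through the programme. Carer-rated scores pass a second such step, after the care has been delivered and experienced.

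If the arms come to differ in whom they succeed in consenting (for example, more consents through a relative for confused patients), the primary scores would compare different kinds of dying patients as well as different care. That could create an apparent effect or hide a real one. Analysing hospitals as randomised does not help, because the selection happens after randomisation. Nor does matching on baseline consent yield, because that value was fixed before the programme began.

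**Working it through.** **1. The plan's own figure.** Inputs from Sample size calculation: difference 3.2 points, effect size 0.55, ICC 0.05, 30 deaths per hospital, two-sided alpha 0.05. The implied SD is 3.2 / 0.55 = 5.82. The design effect is 1 + 29 × 0.05 = 2.45. A cluster t-test with 2(k − 1) degrees of freedom gives 76.0% power with five hospitals per group and 85.1% with six, so six per group is the smallest sufficient number. The same method returns all twelve cells of Table 3. The sample size is not in dispute; it supplies the SD used below.

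**2. Size of a possible bias.** The documents give no consent rates by arm and no effect of case mix on the scores, so these are assumptions. Suppose hard-to-consent patients score 0.3 to 0.5 SD worse, and their share of included deaths differs between arms by 10 to 20 percentage points.

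Bias = share difference × SD difference × SD

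- Low: 0.10 × 0.3 × 5.82 = 0.17 points; 0.17 / 3.2 = 5%.
- High: 0.20 × 0.5 × 5.82 = 0.58 points; 0.58 / 3.2 = 18%.

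Either sign is possible. The answer depends heavily on the assumptions: a factor worth 2 to 5.8 points with a shift of 10 to 30 percentage points would give 0.20 to 1.74 points (6% to 54%).

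**3. Effect on false positives.** With no true effect, six hospitals per arm, 30 deaths each and ICC 0.05:

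| Bias (points) | Two-sided rejection |
|---|---|
| 0 | 5.0% |
| 0.32 | 6.1% |
| 0.64 | 9.3% |

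The high case in step 2, 0.58, lies below the last row.

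**4. What the stated adjustment removes.** Simulation of 4,000 trials with no true effect, six hospitals per arm, 30 patients per hospital and period, and ICC 0.05. It assumes a patient factor worth 3.2 points whose prevalence differs by 20 percentage points between arms (expected bias 0.20 × 3.2 = 0.64).

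| Mean arm estimate (true value 0) | Shift arises after randomisation | Same difference already present at baseline |
|---|---|---|
| Unadjusted | 0.65 | 0.63 |
| Adjusted for hospital baseline average | 0.65 | 0.25 |
| Baseline average plus patient factor | 0.01 | −0.39 |

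The baseline average partly corrects a stable difference and does nothing for a new one. Adding the patient factor removes the new one. The last cell carries a warning: where a difference is already present at baseline, a crude baseline average contains the same case mix, so the combined model corrects for it twice. The baseline average should then be adjusted for the same characteristics.

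**The case against.** The strongest reply is that differential selection is a hypothesis. Consent is to be asked of each patient at admission, before anyone knows who will die, so nurses do not pick deaths to enrol. A relative is asked in both arms when capacity is lacking. Carers who could not be asked get a posted form. Carer consent does not gate the nurse-rated versions of the primary scales. Inclusion by consent was required by the ethics committee. Pair matching and the baseline adjustment deal with part of any stable difference between hospitals. All of this stands. It limits the risk without removing it: the plan itself expects consent yield to vary between wards, and its cluster size allows for deaths that are not included.

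A reader might infer that the programme is meant to change nurses' motivation to obtain consent. The documents do not say so. The Background speaks of awareness of end-of-life care, and motivation appears only in the Randomization section, as a name for baseline consent yield. That nurses know the arm is likewise an inference, from the training in Table 1 and the absence of any described masking.

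A reader might also object that covariates and inclusion counts belong in an analysis plan that is not shown. That has some force. However, the Multivariable analysis section does state an adjustment, and the recruitment process is protocol content. The lack of a significance test between arms on patient characteristics is not a defect.

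**Conclusion.** The concern holds as a risk built into the design. Outcome-year patients and carers are consented after allocation by staff who can be expected to know the arm, and the stated adjustment uses only baseline-period averages. It would leave in the primary estimate any case-mix difference that begins after randomisation.

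The documents do not support the stronger readings that bias is established, that its direction is known, or that the model has no protective adjustment at all. The range of 0.17 to 0.58 points rests on assumed inputs throughout, apart from the SD of 5.82 implied by the plan. At that size the bias would not by itself account for a 3.2-point difference, but it could matter more for a smaller true effect. A modest, inexpensive change is justified.

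**What to change.** 1. In the Multivariable analysis section, add to the primary hierarchical models prespecified patient-level characteristics that the programme cannot affect: for example age, sex, main diagnosis and dementia before admission, where these are recorded for the descriptive table. The article does not list what is recorded, so this must be confirmed. Leave out length of stay and consent route, which the arm may itself influence. Adjust the baseline average for the same characteristics.

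2. Continue after randomisation the counts of deaths and consents per hospital already needed for matching. Report by arm and period the number of eligible deaths (more than 48 hours in hospital), of deaths with patient consent, and of deaths with family carer consent.

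3. State in advance that, if these fractions differ between arms, the result may partly reflect selection. Add recruitment after randomisation to the limitations.

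The cost is some analysis wording, a small continuing count per ward and a few records with missing covariates. Patient-level covariates use no between-hospital degrees of freedom. The adjustment corrects measured case mix only, so the counts are needed as well.

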### Ethical approval

The study is approved by the Central Ethics Committee of the Vrije Universiteit Brussel (VUB) (Belgium) and by the Local Ethics Committees of the participating hospitals in Flanders.

## Discussion

This will be the first cluster randomized controlled trial to evaluate the effectiveness of the Care Programme for the Last Days of Life for the acute geriatric hospital setting. Following a baseline assessment, geriatric hospital wards will be randomized to the intervention or control group where the Care Programme will be implemented or care will be provided as usual. A post-intervention assessment should allow us to detect differences in the symptom frequency and symptom burden between patients in the intervention wards and those in the control wards.

A cluster RCT design has several important strengths. The first advantage of this robust design is that a control group will be used. Working with control hospitals can avoid the situation where differences between the baseline and post- intervention assessments within the intervention group are caused by changes other than the intervention that is being studied. Secondly, in all participating hospital wards the quality of care and the quality of life during the last 48 hours of life will be assessed before and after implementation of the care programme. That means that we will be able to compare end-of-life care in geriatric hospital wards before and after the implementation of our intervention, and that each hospital operates as its own control. A third strength of this design is that cluster randomized trials, unlike individually randomized controlled trials, can reduce the effect of treatment contamination as one or more geriatric wards from one hospital will handle the same care principles [34]. Fourth, this design may also increase compliance due to group participation.

This study also has several limitations. Firstly, the study questionnaires address symptoms and care during the last 48 hours of life, which is more or less the target period of the Care Guide. However, it is unknown how long the geriatric patients will be supported by the Care Guide for the Last Days of Life. Earlier studies have shown that the median duration and average time of use of the LCP in the hospital setting was 16 and 29 hours respectively [35,36]. However, another study found that 44% of hospice patients were supported by the LCP during two days [37]. We therefore cannot preclude that we may be measuring the quality of care during a period when the Care Guide had not yet been put into effect, which could dilute the apparent effect of the Care Programme. A second limitation, inherent to the focus on the last 48 hours of life, is that evaluations of a patient’s quality of life, content of care and communication will depend on after-death evaluations by proxies (nurses, physicians and family carers). However, in selecting the items for the questionnaires, we have taken into account the reliability and validity of proxy-reporting. Proxy measurements have, for instances, been shown to be relatively valid for relatively objective information such as the processes of care [38]. In former retrospective studies, bereaved family carers and professional caregivers, like nurses and physicians, have acted as proxy respondents and the reliability of proxy assessments for various aspects of end-of-life care and quality of life are well described [39]. The aspects we choose to measure are those that have shown sufficient agreement between patients and proxy respondents: observable physical symptoms, evaluation of care, service use and awareness of diagnosis [40]. We will also investigate some aspects that are more subjective such as psychological symptoms. It is known that in comparison with patients, nurses and family carers tend to overestimate the severity of such symptoms whereas physicians tend to underestimate them [39]. We therefore take into account the different perspectives of nurses, physicians and family carers.

Most end-of-life care pathways or programmes such as the LCP have been studied in different healthcare settings and have focused mainly on oncology patients. However, due to the ageing population and a simultaneous increase in the incidence of chronic diseases, future research evaluating the effects of end-of-life care pathways or programmes should also focus on elderly people dying of causes other than cancer [12,8]. Evaluating the Care Programme for the Last Days of Life for the acute geriatric hospital patient would therefore add evidence of the effectiveness of initiatives aimed at improving the quality of life and care for older patients dying in acute geriatric hospital wards.

By using a cluster randomized controlled trial design, the proposed study will contribute substantially to the increase in evidence for end-of-life care interventions. To our knowledge only one other cluster RCT in this area has studied the effects of the LCP programme on cancer patients dying in Italian hospitals [19,20]. A cluster RCT is a challenging, high-risk research design. However, results from a before-after cluster phase 2 trial support the need for multi-centre cluster randomized controlled trials [41], as this is the only feasible method of assessing the effectiveness of end-of-life care interventions [19].

## Conclusions

This will be the first cluster randomized controlled trial aimed at evaluating the effectiveness of the Care Programme for the Last Days of Life to improve the quality of care and quality of life during the last 48 hours of life of patients dying in acute geriatric hospital wards. Using this robust study design will allow us to describe in detail the quality of care and quality of life of elderly people dying in hospitals and will add to the evidence about the effectiveness of the Care Programme in the acute geriatric hospital setting. The poor quality of end-of-life care in hospitals remains a concern and dealing with that problem is a public health priority. We hope that this study will not only show whether the Care Programme for the Last Days of Life is effective in geriatric hospital wards but will also provide an understanding of the contribution of the different components of the Care Programme to end-of life care.

